## Abstract

**Background:**

There is a continuing debate on the desirability of informing patients with cancer and thereby involving them in treatment decisions. On the one hand, information uptake may be hampered, and additional stress could be inflicted by involving these patients. On the other hand, even patients with advanced cancer desire information on risks and prognosis. To settle the debate, a decision aid will be developed and presented to patients with advanced disease at the point of decision making. The aid is used to assess the amount of information desired. Factors related to information desire are explored, as well as the ability of the medical oncologist to judge the patient's information desire. The effects of the information on patient well-being are assessed by comparing the decision aid group with a usual care group.

**Methods/Design:**

This study is a randomized controlled trial of patients with advanced colorectal, breast, or ovarian cancer who have started treatment with first-line palliative chemotherapy. The trial will consist of 100 patients in the decision aid group and 70 patients in the usual care group. To collect complete data of 170 patients, 246 patients will be approached for the study. Patients will complete a baseline questionnaire on sociodemographic data, well-being measures, and psychological measures, believed to predict information desire. The medical oncologist will judge the patient's information desire. After disease progression is diagnosed, the medical oncologist offers the choice between second-line palliative chemotherapy plus best supportive care (BSC) and BSC alone. Randomization will take place to determine whether patients will receive usual care (n = 70) or usual care and the decision aid (n = 100). The aid offers information about the potential risks and benefits of both treatment options, in terms of adverse events, tumour response, and survival. Patients decide for each item whether they desire the information or not. Two follow-up questionnaires will evaluate the effect of the decision aid.

**Discussion:**

This study attempts to settle the debate on the desirability of informing patients with cancer. In contrast to several earlier studies, we will actually deliver information on treatment options to patients at the point of decision making.

**Trial registration:**

Netherlands Trial Register (NTR): NTR1113

## Background

Good clinical practice encompasses optimal providing of information to patients. However, as yet the debate about the desirability of informing patients with cancer and thereby involving them in their own care process has not been resolved. On the one hand, it has been shown that patients with more severe disease may become emotionally unstable and tend to leave decision making to their physician [1-3]. Furthermore, patients with cancer may sometimes deny their illness [4]. In short, patients may wish 'not to know'. All these factors hamper the uptake of information. It is conceivable that additional stress could be inflicted upon patients by involving them in decisions which are complex, emotionally hot, with high personal stakes and have to be taken under time pressure. These circumstances are unfavourable for rational decision making [5]. Taken these arguments together, the positive effects of informing cancer patients with relevant information for treatment decision making can be questioned.

On the other hand, cancer patients desire to be informed about risks and prognosis. A systematic review of Gaston *et al*. (2005) [6] showed that almost all cancer patients wish to be fully informed, regardless of the stage of their disease. Studies using the questionnaire that was developed by Cassileth *et al*. 1980 [7] showed that 83%-92% of advanced cancer patients wanted as much information as possible, whether good or bad [7-10]. Hagerty *et al*. 2004 [11] more specifically explored the desire for prognostic information and showed that over 80% of advanced cancer patients wanted to know the longest time to live with treatment, 5-year survival rates, and average survival. Unlike the aforementioned studies that probed preferences, Elit *et al*. [12] actually delivered information to patients with advanced gynaecological cancer. A decision instrument was used to present information on two chemotherapeutic treatment options and their potential risks and benefits. Survival information was desired by and provided to 92% of the women. However, these patients were asked to make a hypothetical decision, since the treatment choice would not actually be carried out. In the present study, we will assess patients' information desire by offering information in a decision aid at the point of decision making. The treatment choice of patients will actually be carried out.

The amount of information desired may be predicted by a number of patient-related and disease-related factors. It is known that a higher amount of information is preferred by patients who are younger, better educated, have received the diagnosis more recently, and are in a less advanced stage of the disease [7,9,10,13]. In our study, where we actually deliver information using a decision aid, we will examine how various sociodemographic, medical, and psychological characteristics of the patient are related to the patient's information desire.

Current practice of information giving by physicians was investigated by studies in Australia [14,15] and the Netherlands [16], by audio taping the first consult of incurable cancer patients with their oncologists. In both Australia and the Netherlands, the majority of patients were informed about the absence of cure (75% and 84%, respectively). However, information about life expectancy or prognosis was communicated to only 58% and 39% of Australian and Dutch patients, respectively. Only half of the patients in both countries were informed about the alternative to active treatment, best supportive care (BSC). When BSC was mentioned in the Netherlands, half of the time it was mentioned in a single sentence. Obviously, not all information issues were covered in every first consultation. The oncologists may have intuitively tailored the amount and content of information to the individual patient. However, whereas studies have indicated that over 80% of patients desire all information, the percentages of Australian and Dutch patients receiving all information were noticeably lower. This raises the question whether the oncologists may have underestimated the amount of information desired by their patients. In the present study, we will assess whether medical oncologists are able to judge their patients' information desire.

A main concern of physicians is that the provision of prognostic information to seriously ill patients may provoke patient anxiety. Our target population of patients with incurable disease may be particularly anxiety-prone. To address this issue, the effects of the decision aid are evaluated by comparing the decision aid group to a usual care group. The evaluation will examine effects on patient well-being, information and decision related outcomes, and treatment choice.

In conclusion, we aim to settle the debate on the desirability of informing patients with cancer by developing a decision aid to assess the amount of information desired by patients with advanced cancer at the point of decision making. The study population will consist of patients with advanced colorectal, breast, or ovarian cancer who are treated with first-line chemotherapy and upon disease progression will face the choice between two equivalent treatment options. These patients can decide to have second-line chemotherapy in combination with BSC, or they can refrain from further chemotherapy and opt for BSC alone. Second-line chemotherapy may induce tumour response and prolong survival, but also entails a risk of serious adverse events. Our research questions are: 1a) Do these patients want to be informed about the treatment options, and specifically about their prognosis? 1b) Which factors determine whether or not these patients want to be informed? 2) Can the medical oncologist judge whether or not the patient wants the risk information? 3) What is the effect of the decision aid on patient outcomes (well-being, information and decision related outcomes, treatment choice) compared to usual care?

## Methods/Design

### Patients

In 11 hospitals in the Netherlands, all patients with advanced colorectal, breast, or ovarian cancer who have started treatment with first-line palliative chemotherapy and upon disease progression will be faced by the choice regarding second-line palliative chemotherapy will be included. Exclusion criteria are labile personality structure, as assessed by the physicians, a Karnofsky performance score lower than 60, and insufficient knowledge of the Dutch language. The study has been approved by the research ethics committees of all participating hospitals.

### Procedure

The medical oncologist, or a nurse who first consulted the medical oncologist, will inform eligible patients in a general way that this study focuses on 'how to involve the opinion of patients in the treatment'. Next, he or she will ask whether the researcher can contact the patient by phone about this study. The oncologist or nurse is instructed not to discuss that survival information can be provided in the study, in order not to lose patients not desiring such information. After the visit of the patient, the oncologist fills in the medical history on the inclusion form. He or she also makes a judgment whether or not the patient will desire information about adverse events, tumour response, and median survival that will be offered in the interview (research question 2). In the phone call, patients are explained that data are collected by means of three questionnaires and possibly an interview. All patients who agree to participate will provide written informed consent.

Patients will be sent a baseline questionnaire (t1) to collect sociodemographic data, well-being measures, and measures that predict information desire. When tumour progression is diagnosed, second-line chemotherapy will be offered by the oncologist and randomization will be performed. Patients in the usual care group will receive information about the treatment choice from their oncologist. In the intervention group, patients will receive the same information, and will in addition be offered information in an interview using a decision aid. At the moment of disease progression, the medical oncologist is asked to estimate patient survival, because this is expected to be associated with the patient's information desire.

To evaluate the effect of the decision aid, two follow-up questionnaires will be sent to the patients, one week (t2) and eight weeks (t3) after the treatment choice, before the first evaluation of chemotherapy. Figure 1 displays the complete procedure.

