#### Information

The preferred amount of information is measured on a 11-point scale ranging from 0 (I want to know nothing about the illness and its treatment) to 10 (I want to know everything there is to know about the illness and its treatment) [8]. The amount of information received about the treatment choice is measured on a 7-point scale ranging from 1 (I received way too little information), 4 (I received exactly enough information), to 7 (I received way too much information). Information received during the consultation with the oncologist, regarding adverse events, tumour response, and survival, is assessed using a yes/no response. Whether patients received any undesired information is asked with a question using a yes/no response. The key variable information desire is described under 'Interview' above. Satisfaction with the quality of information is asked with three questions related to information on adverse events, tumour response, and survival. Responses are on a 6-point scale ranging from 1 (not satisfied) to 6 (very much satisfied). The balanced presentation of information is evaluated on a 5-point scale from 1 (clearly in favour of chemotherapy plus BSC), 3 (balanced), to 5 (clearly in favour of BSC alone). Six questions are asked about unpleasant, shocking, frightening, and threatening experiences with the information received, measured on a 5-point scale from 1 (no negative experience) to 5 (very negative experience). Numeracy, i.e. the ability to handle basic probability concepts, needed for the interpretation of risk information, is measured by the Subjective Numeracy Scale (SNS) [27].

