### Sample size calculation

Our primary research question is whether or not patients want to be informed. For study question 1a, about 100 patients in the intervention group will suffice to estimate an assumed desire rate for prognostic information of 80% with 95% confidence interval from 71% to 87%. For study question 1b, regarding factors that determine information desire, again about 100 patients will suffice to detect a weak correlation of 0.28 between a predictor and information desire, with α = 0.05 and a power equal to 0.82. For question 2, dealing with the ability of the medical oncologist to judge whether or not the patient wants this information, the same analysis applies as for study question 1b. For study question 3, which addresses the effect of the introduction of decision support compared to usual care on patient well-being, the intervention group is compared to the usual care group. Because one of the main concerns of physicians is that information on prognosis provokes anxiety, anxiety is used as the main outcome measure. We assume that the HADS anxiety difference between the two groups at t3 is equal to 2.2, and the correlation between the measurements at t1 and t3 equals 0.72. The standard deviation in each cell is about 6, corresponding to a medium sized effect size of 0.36. With α = 0.05, and 70 patients in each group, the power to detect the assumed effect is equal to 0.81. In conclusion, 100 patients in the intervention group and 70 patients in the usual care group suffice to answer the above research questions. Assuming that 30% of the patients refuse to give informed consent, and that 1% of patients has died at t3, 246 patients will have to be approached.

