### Statistical Analysis

In all the analyses, scale values will be calculated only if at least half of the items are available, by imputing the mean of the available items. Question 1a about the information desire will be answered by calculating the desire rate for prognostic information with a 95% confidence interval. For question 1b, which factors determine information desire, patients will be grouped according to information desire, ranging from 0 (no information desired) to 3 (information on serious adverse events, tumour response, and survival desired). Then comparisons between these four groups will be made. For categorical variables, the Chi-square test will be used. Continuous data will also be analyzed using the Chi-Square test, after a median-split subdivision into two categories. The HADS scores will be divided by use of a clinical cut-off point of 8 [17,30,31]. Bivariate analyses will be presented with p-value of variables related with information desire at the level of p < 0.2. Finally, these variables will be entered simultaneously in a regression model.

For question 2, agreement between the substitute judgment of the oncologist and the patient information desire is determined. Agreement can arise from chance; a measure correcting for chance agreement is the κ statistic, ranging from 0 to 1. A κ of 0.2, 0.5, and 0.8 indicates poor, moderate, and good agreement, respectively [32,33]. In bivariate and multivariate analyses, associations will be sought between agreement and patient variables (sociodemographic, medical, psychological, knowledge and information). Dichotomized variables associated with agreement at a level of p < 0.2 will be entered simultaneously in a regression model.

Question 3, which addresses the effect of the introduction of decision support compared to usual care on patient well-being, will be answered by comparing the intervention group with the usual care group. Analyses of covariance corrected for differences at baseline are used to test the effect of the intervention. For group comparisons at a single point in time, a t test will be performed for continuous variables and the Chi-square test for categorical variables.

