Randomization is, for practical reasons, performed by using sealed envelopes. In some of the 11 participating hospitals, there will be little time between the diagnosis of disease progression and subsequent consultation with a nurse. Therefore, instant randomization will be required and envelopes are a very practical method to perform this. The use of envelopes leaves a possibility to subvert the randomization procedure. However, a plain attempt to allocate a patient out of sequence will be discovered because the envelopes are sequentially numbered and the allocation can be compared with the predetermined sequence. The oncologist could also decide not to randomize a patient, but this would not go unnoticed since all patients are registered on the trial before the moment of randomization, therefore we will be able to compare patients who were and were not randomized.

Blinding of the medical oncologists and the patients is not feasible in this type of research, because patients may want to discuss the information from the decision aid with their oncologist. However, patients are blinded to the intervention in that they are not aware of the exact content of the decision aid; they are only informed that a new method of information giving is investigated.

A major strength of this study is that, in contrast to many previous studies, we will actually deliver information on treatment options to patients at the point of decision making. The results of this study can be applied to improve the provision of information in daily clinical practice. Generalization to the target population is facilitated by the broad inclusion criteria that are used in this study and the use of the decision aid by various nurses in the 11 participating hospitals. Furthermore, the method used to assess patients' information desire very much resembles information giving in clinical practice, by actually providing information at the moment of the treatment choice.

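### As described, the desire measure cannot separate patients who decline because the oncologist has already told them from patients who wish not to know, so the primary desire rate may be too low

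*Protocol article*

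**What the plan says.** **Order of events.** Under Procedure, at tumour progression "second-line chemotherapy will be offered by the oncologist and randomization will be performed". Usual care patients are informed by their oncologist. For the arm allocated to the aid, the article states: "patients will receive the same information, and will in addition be offered information in an interview using a decision aid". The Abstract gives the same order: the oncologist's offer, then randomization. The section Interview has a nurse or the researcher deliver the aid, and the Discussion notes that in some hospitals "there will be little time between the diagnosis of disease progression and subsequent consultation with a nurse".

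**Measure.** For each of three items (serious adverse events, tumour response, survival) the interviewer explains what kind of information is available and asks whether the patient wants it. The section Information names this answer as the key variable.

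**Analysis.** Under Statistical Analysis, question 1a is a simple rate for prognostic information with a 95% confidence interval. Question 1b groups patients by a score "ranging from 0 (no information desired) to 3 (information on serious adverse events, tumour response, and survival desired". Question 2 compares the same answers with the oncologist's judgment by kappa.

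**Record of earlier information.** "Information received during the consultation with the oncologist, regarding adverse events, tumour response, and survival, is assessed using a yes/no response" (Information). Table 1 places this item at t2 only, which is after the interview.

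**The concern.** The Background sets out the debate as whether patients with advanced cancer wish to know or wish not to know, and the Sample size calculation names this as the primary research question. A patient may decline an item for either of two nearly opposite reasons: not wanting to know, or having just been told. The measure as described gives both the same code.

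Three things could follow:

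- **Question 1a:** the desire rate would understate how many patients want prognostic information.
- **Question 1b:** the groups with low scores would mix patients who avoid information with patients who already have it, which blurs the search for determinants.
- **Selectivity:** the Background suggests that oncologists may adapt what they tell to the individual patient. If so, those who want information are more likely to have been told already, and the misclassification would fall unevenly across patients.

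**Working it through.** **1. The plan's own figure.** Inputs (Sample size calculation): desire rate 80%, n about 100, stated interval 71% to 87%.

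Wilson limits: (p + z²/2n ± z·√(p(1−p)/n + z²/4n²)) / (1 + z²/n), with p = 0.80, n = 100, z = 1.96.

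- Centre: (0.80 + 0.0192) / 1.0384 = 0.789
- Half-width: 1.96 × √(0.0016 + 0.000096) / 1.0384 = 0.078
- Limits: 71.1% to 86.7%

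The exact (Clopper-Pearson) limits are 70.8% to 87.3%. Both round to the stated interval, so the arithmetic is correct. The issue is what the 80% measures.

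**2. Observed 80%: what could the true rate be?** The documents do not say how many second-line patients have already been told their prognosis. The Background gives a figure for first consultations only: "information about life expectancy or prognosis was communicated to only 58% and 39% of Australian and Dutch patients", in that order. I use the Dutch 39% as an illustration and assume that it applies among decliners.

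- Decliners: 100 − 80 = 20
- Decliners already told: 20 × 0.39 = 7.8, about 8
- If none of them declined for that reason, the true rate is 80%
- If all of them did, it is (80 + 7.8) / 100 = 87.8%, about 88%

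With the Australian 58%, the same top end would be (80 + 11.6) / 100 = 91.6%.

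The top end is an extreme case. Of 39 told patients, 31.2 accept and 7.8 decline, so it needs 39 of 39 told patients to want the information. Among the 61 not told, 48.8 accept, which is 80%.

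**3. True 80%: what would be observed?** Let K be the share already told, assumed the same among all who want the information. Let f be the share of those told patients who decline because they already have it. The documents give no value for f, so a range is shown. Observed rate = 0.80 × (1 − K·f).

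| f | K = 39% | K = 58% |
|---|---|---|
| 0.10 | 76.9% | 75.4% |
| 0.25 | 72.2% | 68.4% |
| 0.50 | 64.4% | 56.8% |

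The observed rate drops below 71% once f exceeds (1 − 0.71/0.80)/K, which is 0.29 for K = 39% and 0.19 for K = 58%. At K = 39% and f = 0.25 the shift is 80 − 72.2 = 7.8 points. The planned half-width is (87 − 71)/2 = 8 points. A larger sample would not remove such a shift.

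Steps 2 and 3 are not inverses. Step 2 fixes the told share among decliners, and step 3 fixes it among those who want the information.

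**The case against.** **The order is inferred.** Receiving the interview in addition does not by itself mean receiving it afterwards, and the nurse consultation is said to follow the diagnosis, not a completed account of risks. Figure 1, which shows the procedure, is not available. This stands as a caveat, but the sections cited agree and none points the other way.

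**Being told something is not having what the aid offers.** The aid gives frequencies, pie charts and median survival, and the interviewer explains the kind of information before asking. Many informed patients may still accept. This stands. It limits the size but does not remove the ambiguity for those who decline.

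**The interviewer's form may record reasons.** The article says that the form registers desire and gives a short evaluation of the interview, without listing its items. This also stands, so the point concerns the measure as the article describes it.

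**Question 2.** A reader might infer that kappa is computed against wrong patient values. The documents do not support that. The oncologist judges desire for the information to be offered in the interview, and the reference is the patient's answer to that same offer. Kappa is affected only if the target is a general wish to know.

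**Use of the t2 item.** A reader might also infer that no analysis uses the record of what the oncologist told. For question 2, Statistical Analysis lists information variables among those to be related to agreement, and Table 1 files this item under Information, so it may already enter there. For questions 1a and 1b no such role is named.

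**Conclusion.** The point holds as an ambiguity in how the primary variable is defined. If the interview follows the oncologist's information, as the text indicates, a refusal has two possible meanings that the described measure does not separate. The question 1a rate may be biased downward, and the low-desire groups in question 1b may be mixed.

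The size is unknown. With 80 of 100 accepting and 39% of decliners already told, the true rate lies between 80% and about 88%. A reader might take 88% as the corrected rate, just above the planned interval. It is not an estimate: it requires every already-told patient to want the information, rests on a first-consultation figure and assumes that this figure holds among decliners. The bias could equally be negligible.

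This is a cheap improvement to what question 1a can conclude, not a flaw that invalidates the planned analysis.

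**What to change.** - **Data:** on the interviewer's existing form, add one tick-box after each refused item: do not want to know / already told by my oncologist / other.
- **Primary analyses:** leave questions 1a, 1b and kappa as planned.
- **Sensitivity analyses:** count already-told refusals as desiring the information. This gives an upper bound for the 1a rate. Repeat the 0–3 score and kappa on that coding.
- **The t2 item:** use it only to tabulate the desire rate by whether the oncologist had given the information, and note that it is recalled after the interview. Do not recode refusals from it, because having been told does not show why the patient declined.
- **Avoid:** dropping already-informed decliners while keeping already-informed acceptors. That selects on the outcome, and the rate can only rise. In the illustration it would be 80/(100 − 8) = 87%.

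The cost is one tick-box per refused item and one extra tabulation. The downside is that the reason is self-reported.
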